# The sydney playground project: popping the bubblewrap - unleashing the power of play: a cluster randomized controlled trial of a primary school playground-based intervention aiming to increase children's physical activity and social skills

**DOI:** 10.1186/1471-2458-11-680

**Published:** 2011-09-01

## Abstract

**Background:**

In the Westernised world, numerous children are overweight and have problems with bullying and mental health. One of the underlying causes for all three is postulated to be a decrease in outdoor free play. The aim of the Sydney Playground Project is to demonstrate the effectiveness of two simple interventions aimed to increase children's physical activity and social skills.

**Methods/Design:**

This study protocol describes the design of a 3-year cluster randomised controlled trial (CRCT), in which schools are the clusters. The study consists of a 13-week intervention and 1 week each of pre-and post-testing. We are recruiting 12 schools (6 control; 6 intervention), with 18 randomly chosen participants aged 5 to 7 years in each school. The two intervention strategies are: (1) Child-based intervention: Unstructured materials with no obvious play value introduced to the playground; and (2) Adult-based intervention: Risk reframing sessions held with parents and teachers with the aim of exploring the benefits of allowing children to engage in activities with uncertain outcomes. The primary outcome of the study, physical activity as measured by accelerometer counts, is assessed at baseline and post-intervention. Additional assessments include social skills and interactions, self-concept, after school time use and anthropometric data. Qualitative data (i.e., transcriptions of audio recordings from the risk reframing sessions and of interviews with selected teacher and parent volunteers) are analysed to understand their perceptions of risk in play. The control schools have recess as usual. In addition to outcome evaluation, regular process evaluation sessions are held to monitor fidelity to the treatment.

**Discussion:**

These simple interventions, which could be adopted in every primary school, have the potential of initiating a self-sustaining cycle of prevention for childhood obesity, bullying and mental ill health.

**Trial registration:**

Australian and New Zealand Clinical Trials Registration Number ACTRN12611000089932.

## Background

Disturbing numbers of children in the westernised world are overweight, bullied or have poor mental health. These are all serious childhood problems that are notoriously difficult to treat. Prevention is undoubtedly best, but their continued increase shows how difficult it is to reverse these new and dangerous trends. Burdette and Whitaker [1] suggested a compelling common cause for all three problems: a decrease in outdoor free play. While previous generations spent most of their discretionary time engaged in free play outdoors, today's children play indoors; their free time is often spent in sedentary and solitary activity (e.g., computers, television). Time spent outdoors is often in structured sport rather than in unstructured play that facilitates social interaction and physical activity. Physical activity promotes energy expenditure and has additional benefits such as improved cardiovascular health and gross motor skills. However, less obvious is the role of free play in children's social, emotional and cognitive development. The shift from outdoor play to indoor activities, combined with an increased push for academic achievements, potentially leave children more stressed and with poorer mental health [1]. Most young children love active outdoor play but parents, teachers and carers may limit this, fearing injury or misadventure.

### The issues

#### Risk aversion in the short term can lead to greater risks in the long term

Adult fears are often disproportionate to actual risk: while children can be injured when playing outdoors, most are minor cuts and bruises. On the other hand, restricting children's outdoor play activities may have unintended consequences, such as reducing children's opportunities for reasonable, age-appropriate risk-taking. Fear of litigation results in minimising "risk" at all cost and decreasing the value of "real play" that occurs on school playgrounds [2,3]. Several schools have now placed a ban on running on the school playground [4,5]. Thus, "surplus safety" may result in exactly the negative outcomes it was meant to avert [6]. Although no research has directly examined risk avoidance and children's health outcomes, recent Australian data suggest that concern with children's risk exposure can lead to constraints on children's habitual physical activity, which may have negative public health outcomes [7]. Further, when children perceive that play settings are not demanding enough, they may compensate by engaging in activities that yield challenges -- in the context of undesirable behaviour (e.g., bullying or using play equipment in truly dangerous ways)[8].

#### Social and Physical Environments Affect Play

Opportunities to engage in spontaneous play in the local neighbourhood have declined in recent generations [9]. The age at which children are allowed outside to play on their own has increased in recent years [10]. While parents of older children may have greater tolerance for allowing their children to take manageable risks, young children are generally not allowed to engage in what parents perceive as risky play or activities. Mullins and colleagues [11] speculated that parents are less likely to engage in overt overprotective behaviours as their children reach adolescence, yet still perceive their child as vulnerable. Children are often driven by car to play activities [12] and these activities are likely to be adult-organised and indoors [13]. When children are allowed to play outside, it is often on the school playground for which rules limit play behaviours [14] and purpose-built equipment (e.g., slide) fails to promote collaborative and imaginative play. Slides and climbers are also the source of most serious playground injuries [15] and climbers are often places in which less physically competent children are teased by peers [16].

In contrast, natural play spaces (e.g., woods, gardens) and playgrounds with unstructured construction materials stimulate diverse and creative play [17]. Fantasy and socialisation are prominent and the social hierarchy is based on the ability to imagine what the space might become rather than on physical prowess [18]. Children experience active play through lifting, pushing, and pulling. They engage in creative, socially interactive play as they construct new structures and play within them [19]. Both in our pilot study [20,21], and in a study at another Australian school where children played with unstructured materials, reports of injuries, bullying and fighting were almost non-existent [14].

#### Sedentary lifestyle and obesity

In Australia over 200,000 children are obese [22]. Childhood obesity is a serious problem with a range of significant medical, psychosocial and economic consequences [23]. Despite the growing awareness of the consequences, the prevalence of childhood overweight and obesity is still high in many westernised and westernising countries [24,25]. Regular physical activity is associated with both a longer and healthier life [26], including a decreased risk of obesity [27], insulin resistance [28] and metabolic risk [29]. Similarly, physical *inactivity *during the early years of life is a major contributor to serious medical conditions in children [30,31]. Time spent participating in sedentary and low energy-expending activities is associated with higher relative weight [32-34] and poorer health. Hence, a reduction in sedentary behaviour is important for promoting health [35].

Several underlying issues may contribute to the increasingly sedentary lifestyles of some children. In many cases children are reliant on parents when it comes to the activities they undertake. Families live exceedingly busy lives with limited time for children's free play and unstructured activity. To "make the most" of the time they have, many middle-class parents enrol children in organised activity and sport [36,37] that offer strictly scheduled, structured exercise and play. In families with fewer financial resources, children are more likely to spend more time in front of the television instead [36]. To make sure children's school results do not suffer, there is an increased emphasis on academic tasks, particularly in middle and upper class families. This increased pressure on children, in combination with the perception that there are many "predators" in public spaces, ensures an increase in screen- and homework time and a decrease in time spent outdoors. To save time and keep children "safe," many parents drive them to school and sport--creating a self perpetuating cycle.

#### Mental ill health and bullying

About 14% of Australian children have significant mental health problems [38]. In children from disadvantaged backgrounds, this figure can rise up to 60% [39]. Play is one of the best ways for children to develop coping skills, and thereby mental health. Play engages children's intrinsic motivation and supports autonomy, competence and relatedness that have been shown to promote psychological wellbeing [40].

Poor social skills have been linked both to bullying and being bullied [41] and children with higher self-concept are bullied less often and also are actively included in play more often [42,43]. Our conjecture is that unstructured materials on the playground will give children who are not very sporty or physically coordinated the chance to play. Teachers participating in our pilot study reported that the unstructured materials promoted play between children who had not played together previously--including children who had formerly been excluded [44].

#### Play as an alternative intervention

Play is a universal and profound process that has evolved in both animals and humans. It is spontaneous, exploratory and intrinsically motivated [45]. Children love to explore and delight in opportunities to devise their own free play to experience sheer joy and pleasure in the moment [46]. There are many documented benefits to play [47] and this study aims to engage children's playful nature to promote greater physical activity and to enhance social skill development. When children play freely with materials that are intriguing and that also require physical exertion, we believe that they will spend more time engaging in the activity and thus also be more active for longer periods of time. When materials are large, a little unwieldy, or a bit heavy, it is possible that, in addition to expending more energy, and exerting greater effort, they will recruit help from other children, thus promoting social negotiation in the context of creative play (i.e., what can *we *do with these materials?). Play also offers opportunities for children to take manageable risks and to experience the benefits of a variety of challenges (e.g., motor, social, emotional and cognitive). The playground based intervention presented here is aimed at appealing to children's inherent will to play, rather than imposing a structured program or regimen.

Prevention strategies that target the population as a whole, rather than focussing only on children at risk are preferable. It is difficult to identify who is at risk and all children benefit from increased activity independent of body composition and interest [48]. Thus programs conducted at schools can be highly beneficial.

Previous studies have supported play and changes to the playground as a way of increasing activity. In the UK, painting lines on the playground to promote active games resulted in small but significant and lasting increases in children's physical activity [49-51]. Placing play equipment and activity cards on school playgrounds in Belgium significantly increased the children's moderate to vigorous physical activity (MVPA) [52]. Similar results were found in North Carolina where portable play equipment, including skipping ropes and hula hoops, at day care facilities increased physical activity [53]. Turning a Canadian school playground into a natural play space also increased physical activity significantly [54]. The same group of researchers also found that a higher percentage of children were engaged in MVPA on green areas and on fixed playground equipment than on sporting courts and other courtyards [55].

A few previous researchers have introduced unstructured materials to school playgrounds and studied the effect on social interaction and play. One of them is a Play Pods study, carried out in Bristol from 2006 to 2009 [56]. The overall impression of the outcomes, determined by observations and interviews with children and school staff, was very positive. The researchers observed that the loose items improved children's participation, decision making skills and their control of play within school setting, as well as improved access for all children to inclusive play opportunities. We build on studies such as this with quantitative data.

## Aims and hypotheses

The aim of the Sydney Playground Project is to demonstrate the effectiveness of a simple, cost-effective two-part intervention to increase children's physical activity, social skills and resilience by altering their experience on the school playground. The two intervention strategies are:

a. Child-based intervention: Recycled unstructured materials are placed on the school playground with the aim of increasing physical activity and social skills through unstructured free play.

b. Adult-based intervention: Risk reframing sessions held with parents and teachers with the aim of exploring the benefits of allowing children to engage in activities with uncertain outcomes.

## Methods/Design

### Overall study design

The design of this 3-year study is a cluster randomised controlled trial (CRCT) in which the participating schools are the clusters. The study consists of a 13-week intervention with baseline and post-testing (See Figure 1). The study has been approved by the Human Research Ethics Committee at the University of Sydney and by the Catholic Education Office of the Archdiocese of Sydney.

**Figure 1 F1:**
[figure not shown]
**Study design of Sydney Playground Project**.

### Participants and recruitment

Catholic co-educational primary schools are approached to participate in the study, through emails, phone calls and on-site visits to the principal and/or assistant principal. The schools are located within a 30 km radius of the University of Sydney's Health Sciences campus at Lidcombe, near Sydney. Recruitment continues until 12 schools agree to participate.

### School selection

All participating schools must agree to be randomised into the control or intervention group and refrain from engaging in other new interventions designed to increase activity levels. They continue with normal recess and physical education. There are no exclusion criteria.

### Child selection

Within each school, a random sample of children is invited to participate. Children are selected using the following procedure: To maintain confidentiality, schools assign each of their Kindergarten and Year 1 students (aged 5 to 7 years) a number. Schools are then presented with a set of randomly generated numbers. School staff approach children assigned to the random numbers until 20 students and their parents consent to participate. Data are gathered on country of birth of children and parents as well as languages spoken. Families are approached only if the parents can speak and understand spoken and written English to a degree sufficient to allow them to complete the questionnaires and participate in the risk reframing intervention. Children are included regardless of known disability.

### Sample size

Sample size calculation involves deciding on both the number of schools (clusters) and number of children per school. The desired number of schools provides sufficient cluster-level data for subsequent analyses but, at the same time, is manageable in terms of implementation and data collection. We have selected 12 schools (6 control, 6 intervention) to meet these criteria.

The number of children needed per school is estimated by considering the amount of change from the intervention and correcting for the possibility that children at the same school affect one another's activity levels (determined by intra-cluster correlation [ICC]) We estimated the effect size from the intervention conservatively at 0.5 standard deviations (SD) based on a report that young children engage in moderate to vigorous playground activity 26% of the time and that 40% would be a realistic health-promoting target [57].

With *p *= 0.05, power = 80% and an ICC of .04, we require 18 children per school to show that an effect size of 0.5 SD is significant between groups. This reflects a 68% inflation in sample size over the number that would be required if no adjustment were made for cluster effect (64 vs. 108 participants/group).

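### The stated 80% power leaves out that only 12 schools are randomised: on 10 degrees of freedom the same inputs give about 72% power for 0.5 SD, and 80% is reached only at about 0.55 SD

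*Protocol article*

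**What the plan says.** The Sample size section of the protocol article first fixes the number of schools: "We have selected 12 schools (6 control, 6 intervention) to meet these criteria". The criteria are enough data at school level and a manageable workload; on the first it says "The desired number of schools provides sufficient cluster-level data for subsequent analyses". It then derives the number of children from a significance level of 0.05 and an effect of 0.5 SD: "power = 80% and an ICC of .04, we require 18 children per school". The only adjustment for clustering that it describes is a 68% increase, from 64 to 108 participants per group.

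Two other sections bear on this. Child selection says that recruitment in each school goes on "until 20 students and their parents consent to participate", two more than the 18 in the calculation; no dropout rate is given. Data analysis plans a mixed-effects multilevel regression that allows for clustering and repeated measurement and compares change from baseline between the groups.

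**The concern.** Multiplying an individually randomised sample size by the design effect is a large-sample device. It sets the variance of the treatment difference correctly but keeps the degrees of freedom of the individual-level test, here 2 × 64 − 2 = 126. In this trial treatment is assigned to schools, so the error against which it is tested is estimated from the variation among school means: 12 − 2 = 10 degrees of freedom. With so few clusters the difference is not negligible.

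At stake is how the primary result is read. A non-significant difference in physical activity would be taken to come from a trial with a 20% type II error for 0.5 SD, when the stated inputs imply about 28%. Nor can the power be kept by ignoring the issue at analysis: a normal critical value of 1.96 applied to a statistic with 10 df has a two-sided type I error of about 7.8%, not 5%.

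**Working it through.** **Inputs**, all from the Sample size section: alpha 0.05; power 80%; ICC 0.04; effect 0.5 SD (so SD = 1); k = 6 schools per arm; m = 18 children per school. Sidedness is not stated, but 64 per group is what a two-sided test gives. The sensitivity case m = 20 comes from Child selection.

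**1. Reproducing the article's figure**

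- Two-sided two-sample t test, 0.5 SD, 80% power: n = 63.77, so 64 per group.
- Design effect: 1 + (18 − 1) × 0.04 = 1.68, the 68% increase.
- 64 × 1.68 = 107.5, so 108 = 6 × 18.
- Solved for cluster size with k = 6: m = n(1 − ICC)/(k − n × ICC) = 64 × 0.96/(6 − 64 × 0.04) = 61.44/3.44 = 17.9, so 18.
- Power at 6 × 18 per arm: 80.9% with a normal reference, 80.6% with t on 216 − 2 = 214 df.

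The stated figures therefore reproduce, and the stated 80% belongs to a large-sample reference distribution.

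**2. The same design on school-level degrees of freedom**

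- Var(difference) = (2/k) × [ICC + (1 − ICC)/m] = (2/6) × (0.04 + 0.96/18) = 0.0311.
- SE = √0.0311 = 0.1764.
- Noncentrality = 0.5/0.1764 = 2.83.
- df = 2 × (6 − 1) = 10; two-sided 5% critical value 2.228.
- Power from the noncentral t distribution: **72.4%**. A simulation of 200,000 trials with a t test on school means gave 72.6%.

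**3. Detectable effect and what 80% would take**

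| Design (ICC 0.04) | df | Power at 0.5 SD | Effect detectable at 80% |
|---|---|---|---|
| 6 schools per arm, 18 children | 10 | 72.4% | 0.549 SD |
| 6 schools per arm, 20 children | 10 | 74.9% | 0.533 SD |
| 6 schools per arm, 25 children | 10 | 79.6% | – |
| 6 schools per arm, 26 children | 10 | 80.3% | – |
| 7 schools per arm, 18 children | 12 | 80.2% | – |

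**4. Sensitivity to the ICC** (18 children, 10 df): 81.6% at 0.02, 76.9% at 0.03, 72.4% at 0.04, 68.3% at 0.05 and 52.4% at 0.10.

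**5. Sensitivity to use of the baseline.** The article gives no baseline to follow-up correlation r, so these values are assumptions. They take the same r at child and school level and 0.5 SD in units of the follow-up outcome. The variance is multiplied by 1 − r² for baseline adjustment (9 df) and by 2(1 − r) for change scores (10 df).

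| r | Baseline-adjusted, 9 df | Change score, 10 df |
|---|---|---|
| 0.3 | 75.3% | 58.0% |
| 0.4 | 78.6% | – |
| 0.5 | 82.9% | 72.4% |
| 0.6 | 88.2% | 81.4% |

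**The case against.** The strongest reply is that 72.4% is the power of an unadjusted comparison of follow-up school means, which is not the planned analysis. The Data analysis section plans a mixed model that uses the baseline, and with baseline adjustment and r = 0.5 the power would be 82.9%. This stands as a limit on the claim: the power of the planned analysis is not known from the article. It does not rescue the stated 80%, because the sample size calculation neither states nor uses a correlation. The analysis is also described in terms of change, and change scores could do worse as well as better (58.0% at r = 0.3). If the 0.5 SD and the ICC were already meant for change, 72.4% stands as it is. Analysing individual data in a mixed model does not by itself add degrees of freedom for an effect that varies only between schools.

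Second, the 64, the 1.68 and the 108 are each correct, so this is a choice of approximation rather than a slip in multiplication. That is true. The error lies in the power attached to those numbers.

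Third, the ICC is given without a source, and a change of 0.01 moves power by about four points, so a corrected figure is not precise either. That too is true, but it is a reason to show a range, not to leave a figure that fails at the article's own ICC. A one-sided 5% test on 10 df would give 83.9%, but 64 per group does not match a one-sided test.

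Last, the shortfall is modest, 0.55 against 0.50 SD, and a reported confidence interval would limit misreading of a null result. That bears on how much harm follows, not on whether the statement is right.

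**Conclusion.** The concern holds. Under the article's own inputs (6 + 6 schools, 18 children each, ICC 0.04, 0.5 SD, two-sided 5%), power is 72.4%, not 80%; the type II error is about 28%, and 80% power is reached only at 0.549 SD. The two extra children per school do not close the gap even if every one of them is analysed (74.9%, 0.533 SD). The result assumes equal cluster sizes, a t reference on 10 df and no gain from the baseline. A favourable baseline correlation could bring the planned analysis above 80%, but the article does not make that case.

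**What to change.** Replace the power statement in the Sample size section with one that matches the design, for example: with six schools per arm, 18 children per school, an ICC of 0.04 and a two-sided 5% t test on 10 df, power is 72% for a difference of 0.5 SD, and the difference detectable with 80% power is 0.55 SD.

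If the primary analysis is to adjust for baseline, state the power on that basis instead, with the assumed correlation and degrees of freedom (for example about 83% at r = 0.5 on 9 df) and a range around it. A short ICC range, such as 0.02 to 0.10, would help the reader either way.

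The cost is one sentence and a less favourable stated power. No extra enrolment is needed to make the statement correct. If 80% for 0.5 SD without baseline adjustment is to be kept as the target, it would take 26 children per school or 7 schools per arm.
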